### Process variables

Process variables will be collected to investigate the implementation and maintenance, unexpected pathways and consequences, and mechanisms of impact of MOSAIC.

Attendance at MOSAIC sessions will be recorded by the trial physiotherapists. Adherence to walking goals will be assessed by the 6-item Exercise Adherence Rating Scale^53 54^ at 3 and 6-month follow-up.

Fidelity to the MOSAIC intervention will be assessed in a random subset of ≥10% of the audio-recorded MOSAIC sessions/physiotherapist by two independent raters using bespoke, standardised checklists.

The type and duration of usual care and non-NHS care received by both groups will be recorded using the modified Client Service Receipt Inventory^36^ to evaluate unexpected pathways and consequences.

Proposed mechanisms of impact include changes to theoretically defined sociocognitive variables targeted by MOSAIC. The Brief Illness Perception Questionnaire (a 9-item measure of individuals’ representation of their illness as defined by the common-sense model),^55^ the Theory of Planned Behaviour Questionnaire (a 12-item measure of goals and beliefs about walking as treatment for intermittent claudication)^32^ and the action planning and action control scale (a self-regulation questionnaire)^56 57^ will be assessed at each time point.

### Resource use variables

The study is an important opportunity to assess the feasibility of collecting data on resource use in adults with intermittent claudication to inform future trials. A modified Client Service Receipt Inventory^36^ will be used to record information on service utilisation, income, accommodation and other cost-related variables at all time points to determine completion rates and redundant questions.

### Qualitative study

To explore the experience of MOSAIC treatment and participation in the trial, semistructured, audio-recorded interviews will be conducted with up to 30 participants or until data saturation of themes is reached. A purposive sampling strategy will ensure that a range of participants are selected (eg, age, symptoms, group allocation and recruitment site). Interviews will be conducted via telephone or face to face (depending on participant preference) after completion of the final assessment. A subsample of physiotherapists will be interviewed to explore their experiences of training and delivering MOSAIC by an independent researcher, supported by experienced qualitative researchers in the trial team.^12 13 58 59^ Interview schedules will be developed iteratively, and the questions asked may develop as insights from ongoing interviews and analyses reveal additional areas of relevance. Interviews will be transcribed verbatim, anonymised and analysed thematically by one researcher.^60^ The initial codes will be cross-referenced with a second researcher and the development of themes will be discussed with the trial team to provide different perspectives on coding. Themes will be presented to a sample of interviewees to ensure resonance and plausibility of the themes.

## Patient and public involvement

User involvement is central to the design and management of the MOSAIC trial. Patients were involved in the identification of the research question and two patient advisers reviewed the protocol and assisted in the development of all patient-related materials. One patient adviser is a funding coapplicant. Our patient advisers will be members of the trial management group, contribute to the trial physiotherapist training and dissemination. All participants will be invited to request study results, if interested.

## Data and statistical analysis plan

### Sample size

Based on previous work,^61^ 192 participants will be required to detect a mean 6MWD difference of 58 m (SD=111; α=0.05, 1-β=0.90), accounting for 20% attrition at 3-month follow-up.

### Statistical analysis

A statistical analysis plan will be written by the trial statistician (SE) and agreed with the trial management group and joint trial steering committee/data monitoring and ethics committee. Analyses of primary and secondary outcomes and process variables will be conducted on an intention-to-treat basis and all included participants will be analysed as randomised.

The primary outcome will be analysed using multiple regression and adjusted for baseline 6MWD and site. Results will be reported as the difference in mean 6MWD between the intervention and control groups with 95% CIs. Other continuous outcomes and process variables will be similarly analysed. If appropriate, a mediation analysis using linear regression will examine mechanisms of impact.

Descriptive statistics for sociodemographic and clinical characteristics, attendance at MOSAIC sessions, adherence to treatment and referral to or uptake of other treatments will be computed. Adverse events and serious adverse events will be described.

To determine the MCID, change scores for the five clinical measures will be calculated by subtracting the baseline result from the follow-up results for each participant. Correlations will be computed for participant self-assessment of performance scores and change in clinical outcomes. The mean change in scores for participants reporting no change, small improvement and substantial improvement will be compared by analysis of variance. The sensitivity and specificity for change in score to distinguish participants classified as changed (≥2) from those whose performance was unchanged (−1 to +1) will be calculated and a receiver operating characteristic curve obtained.^62^ The data point corresponding to the upper left corner of the curve will represent the MCID.

As a sensitivity analysis, the MCID will be also calculated using a distribution-based approach. The SE of measurement for all participants scores will be used to estimate the MCID based on the following equation: $\sigma_{1}\surd (1-r)$ where $\sigma_{1}$ is the baseline SD and r represents the intraclass correlation coefficient, which is a measure of the test–retest reliability of the scale. The intraclass correlation coefficient will be calculated using the baseline and follow-up scores for each participant. Using this method, 1 SE of measurement represents the estimated MCID.^63^

If the proportion of missing data is above 10%, multiple imputation will be considered as a sensitivity analysis for the primary outcome, and for the secondary outcomes used in the 3 and 6-month MCID.^64^

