### Objectives

The primary objective is to answer the question: Does MOSAIC improve walking ability (measured by the 6 min walking distance, 6MWD) at the primary endpoint of 3 months compared with usual care in older adults with intermittent claudication?

The secondary objectives include answering the questions:

Does MOSAIC improve (a) activities of daily living and quality of life (QoL) at 3 months and (b) walking ability, activities of daily living and QoL at 6 months compared with usual care in older adults with intermittent claudication?Is it feasible to collect resource use data using a modified measure in older adults with intermittent claudication?What are the minimal clinically important difference (MCID) values for the clinical assessments used for older adults with intermittent claudication?

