### Secondary outcome measures

Other measures will be used to assess the broader effects of the MOSAIC intervention.

Maximal walking ability (duration walked before resting (seconds)) and pain-free walking ability (duration walked before reported pain onset (seconds)) will be recorded during the 6 min walk test.^42 43^ These parameters evaluate the global and integrated physiological responses of all systems involved with exercise and symptom manifestation.

Self-reported maximal walking distance (SR-MWD) will be measured by one global item: ‘What is the maximum distance (in metres) you can walk at your usual pace on a flat surface before leg pain forces you to stop?’^44^ and the 4-item Walking Estimated-Limitation Calculated by History questionnaire (WELCH).^45 46^

Nottingham Extended Activities of Daily Living scale (NEADL)^47 48^ is a 22-item measure with 4 subscales (mobility, kitchen tasks, domestic tasks and leisure activities) and will assess function.

The 6-item disease specific Vascular Quality of Life Questionnaire-6 (VascuQol-6)^49^ and the EQ-5D-5L will assess QoL.^50^

The 7-item Brief IPAQ will estimate daily physical activity.^35^

Adverse events will be recorded by asking participants a single open-ended item: ‘Have you had any problems since your last assessment?’ at 3 and 6-month follow-up. Trial physiotherapists will also report any adverse events in participants randomised to receive the MOSAIC intervention.

To determine the MCID, participants will provide a global rating of change score after five measures (6MWD, SR-MWD, WELCH, NEADL and VascuQoL-6) at the 3 and 6-month follow-up assessments. In response to the question: ‘Has there been any change in your walking ability/walking distance/daily activities etc since the last test?’ participants will be asked to rate their perceived change on a transitional three-point scale (1, worse; 2, about the same; 3, better). If they indicate no change, the participant will score 0. If they indicate there has been an improvement or deterioration, they will be asked to score their change on a 15-point Likert scale: (−7=a very great deal worse to 7=a very great deal better). Scores of −1, 0 and 1 will be considered no change, scores of 2–3 small improvement and scores of 4–7 substantial improvement.^51 52^

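### The ROC rule for the MCID pools small and substantial improvers, so a threshold labelled minimal moves with the share of substantial improvers

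*Protocol article*

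**What the plan says.** Under Objectives, the protocol article lists as a secondary question: "What are the minimal clinically important difference (MCID) values for the clinical assessments used for older adults with intermittent claudication".

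Under Secondary outcome measures, participants give a global rating of change from −7 to 7 after each of five measures (6MWD, SR-MWD, WELCH, NEADL and VascuQoL-6). The ratings are then classed: "Scores of −1, 0 and 1 will be considered no change, scores of 2–3 small improvement and scores of 4–7 substantial improvement".

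Under Statistical analysis, the classes are used in two ways.

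- In an ANOVA they stay apart: "The mean change in scores for participants reporting no change, small improvement and substantial improvement will be compared by analysis of variance".
- In the ROC analysis the change score is used "to distinguish participants classified as changed (≥2) from those whose performance was unchanged". The positive class is everyone rated 2 or more, and the reference class is "those whose performance was unchanged (−1 to +1) will be calculated and a receiver operating characteristic curve obtained". The decision rule follows: "The data point corresponding to the upper left corner of the curve will represent the MCID".

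The one stated sensitivity analysis for the MCID is distribution-based (1 SE of measurement).

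**The concern.** The quantity sought is a minimal difference, and the plan has already defined a class of people who improved by a small amount. The rule that produces the MCID does not use that class. It takes ratings 2 to 7 together, so people whom the plan calls substantially improved help to set the minimal threshold.

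Two samples with the same change score at every rating level would then give different MCIDs if they differed in their mix of small and substantial improvers. Reported MCIDs tend to be reused outside the trial that produced them, so a reader needs to know which contrast a value came from and how far it depends on that mix. Nothing else in the plan shows this. The ANOVA compares means and yields no cut-point, and the 1-SEM analysis does not use the ratings at all. The same rule serves all five measures.

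**Working it through.** **The plan's own figures.** No numeric MCID is stated. The only figure that can be reproduced is the sample size, used here solely to fix a realistic number of evaluable participants. The plan says: "192 participants will be required to detect a mean 6MWD difference of 58 m (SD=111; α=0.05, 1-β=0.90), accounting for 20% attrition". With two-sided α, n per arm = 2 × (1.960 + 1.282)² × (111/58)² ≈ 77, so 154 in total; 154/0.8 = 192.5. The stated 192 agrees within rounding.

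**Where the upper-left point falls.** Let change be N(0, s) in the unchanged, N(m₁, s) in small improvers and N(m₂, s) in substantial improvers. Let w be the share of substantial improvers among those rated 2 or more. At cut-point c:

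- 1 − specificity = 1 − Φ(c/s)
- 1 − sensitivity = (1 − w) Φ((c − m₁)/s) + w Φ((c − m₂)/s)

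The upper-left point minimises (1 − sensitivity)² + (1 − specificity)². With w = 0 the problem is symmetric and c = m₁/2. With w = 1, c = m₂/2. For w in between, c lies between these two and rises with w in every scenario below.

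**Inputs.** The document gives none of m₁, m₂, s or w, so all are assumptions: m₁ = 20–30 m, m₂ = 50–75 m, s = 30 or 50 m, w = 0.25–0.75.

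**Cut-points in metres for 6MWD change (ratio to the small-only point in brackets).**

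| s | m₁, m₂ | w = 0 | w = 0.25 | w = 0.50 | w = 0.75 |
|---|---|---|---|---|---|
| 30 | 20, 50 | 10.0 | 13.7 (1.37) | 17.5 (1.75) | 21.3 (2.13) |
| 30 | 20, 60 | 10.0 | 14.7 (1.47) | 19.7 (1.97) | 24.9 (2.49) |
| 30 | 30, 60 | 15.0 | 18.4 (1.23) | 22.1 (1.47) | 25.9 (1.73) |
| 30 | 25, 75 | 12.5 | 17.5 (1.40) | 23.4 (1.88) | 30.2 (2.41) |
| 50 | 20, 50 | 10.0 | 14.1 (1.41) | 17.9 (1.79) | 21.6 (2.16) |
| 50 | 20, 60 | 10.0 | 15.5 (1.55) | 20.6 (2.06) | 25.5 (2.55) |
| 50 | 30, 60 | 15.0 | 18.9 (1.26) | 22.7 (1.52) | 26.4 (1.76) |
| 50 | 25, 75 | 12.5 | 19.0 (1.52) | 25.5 (2.04) | 31.6 (2.53) |

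The small-only point is 10–15 m. With half of improvers substantial it is 17.5–25.5 m, or 1.47 to 2.06 times. Over all shares the ratio runs from 1.23 to 2.55. The Youden point shows the same pattern: in SD units with m₁ = 0.5 and m₂ = 1.0 it is 0.25, 0.34, 0.41 and 0.46 at w = 0, 0.25, 0.50 and 0.75.

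**Against sampling error.** A simulation with 154 evaluable participants, half rated 2 or more, m₁ = 0.5 and m₂ = 1.0 SD gave mean cut-points of 0.26, 0.32, 0.39 and 0.45 SD at the same four shares, with a sampling SD of about 0.19. Moving from w = 0 to w = 0.50 shifts the point by 0.39 − 0.26 = 0.13 SD. That is less than one sampling SD, but it is systematic and would not shrink with more data.

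**A second benchmark.** The mean change in small improvers, which the ANOVA will show, is m₁. The small-only ROC point is m₁/2. In all 24 pooled cells of the table, the planned point is closer to m₁ than m₁/2 is. At w = 0.25 or 0.50 it is below m₁ or at most 0.6 m above it. At w = 0.75 it exceeds m₁ by at most 6.6 m, and in the two scenarios with m₁ = 30 it stays below.

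**The case against.** The strongest reply is that the pooled contrast answers a coherent question: which change score best separates anyone at least slightly improved from the unchanged? Its boundary sits at the lowest rating counted as improvement, and the plan cites a source for the method that is not available here. On this view the choice is one of estimand, and the document does not contradict itself. That stands, and it is why the planned contrast should be kept. It does not explain why the result is labelled minimal when a small-improvement class has been defined.

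A reader might infer that the planned MCID is inflated, or biased upward. The documents do not support that. The ratios in the table are relative to the small-only ROC point, and no truth is given against which to measure bias. Taking the small-improver mean as the benchmark instead, the planned point is nearer than the small-only point in every scenario.

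A reader might also infer that a successful MOSAIC would raise the bar by which it is judged. The trial is judged on the adjusted mean 6MWD difference with its 95% CI and is sized on 58 m; no responder criterion based on the MCID appears. Nor does the number of improvers matter by itself. A ROC curve does not depend on the overall proportion improved, only on the mix within the group rated 2 or more.

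Finally, replacing the pooled contrast would not clearly help in a trial of this size. Even if the small-only point is taken as the target, simulated RMSE for the planned and the small-only contrast was 0.197 and 0.203, 0.225 and 0.222, and 0.266 and 0.285 SD at shares of 0.25, 0.50 and 0.75 (means 0.5 and 1.0 SD). The small-only contrast won clearly only when substantial improvers changed about three times as much (0.315 against 0.233 at a share of 0.50). This stands as an argument for adding the second contrast and not substituting it.

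**Conclusion.** The concern holds in a limited form. The plan defines the MCID by one ROC cut-point that moves with the share of participants the plan itself calls substantially improved, and no other planned analysis gives a threshold for small improvement. The direction rests on one assumption, implied by the class labels: substantial improvers change more on average than small improvers. The size, about 1.2 to 2.6 times the small-only point, rests on normal change scores with a common SD and on means, SDs and shares that the document does not supply. It measures sensitivity to the choice of contrast, not bias. The primary 6MWD comparison and the sample size are unaffected.

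**What to change.** In the analysis plan, for each of the five measures:

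- add a ROC contrast of small improvement (2–3) versus unchanged (−1 to +1);
- keep the planned contrast of ≥2 versus unchanged, labelled as the threshold for any improvement;
- report both cut-points with confidence intervals, beside the ANOVA mean change in the small-improvement class and the number of participants in each class.

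This takes a sentence or two and no new data, since the ratings are already collected on the 15-point scale. The cost is that the small-only cut-point rests on fewer participants and will have a wider interval; reporting the two together lets the reader see that trade-off.

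### The ROC rule calls its upper-left point the MCID without condition, so a measure whose change score is unrelated to patients' ratings still receives one, near the mean change in the sample

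*Protocol article*

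**What the plan says.** The protocol article lists the MCID among its secondary questions (Objectives): "What are the minimal clinically important difference (MCID) values for the clinical assessments used for older adults with intermittent claudication"? Under Secondary outcome measures, "participants will provide a global rating of change score after five measures (6MWD, SR-MWD, WELCH, NEADL and VascuQoL-6"), at both follow-ups.

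The Statistical analysis section then sets out these steps:

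- An association check: "Correlations will be computed for participant self-assessment of performance scores and change in clinical outcomes".
- A comparison of rating groups: "The mean change in scores for participants reporting no change, small improvement and substantial improvement will be compared by analysis of variance".
- Sensitivity, specificity and a ROC curve for the change score, to "distinguish participants classified as changed (≥2) from those whose performance was unchanged (−1 to +1").
- The decision: "The data point corresponding to the upper left corner of the curve will represent the MCID".
- A second method: "As a sensitivity analysis, the MCID will be also calculated using a distribution-based approach", using one standard error of measurement.

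No minimum AUC, correlation or precision is attached to the decision sentence, and no consequence follows from a weak correlation or a flat analysis of variance. The same section says that a separate SAP will be written; it is not shown.

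**The concern.** An anchor-based MCID has meaning only if the anchor, here the patient's rating of change, is related to the change score. The decision sentence does not depend on that. Whenever both rating classes are present, some point lies closest to the upper-left corner, so the rule cannot end in the answer that no MCID could be established.

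Without an association, the chosen cut-off describes how far the sample moved on average, including any treatment effect, and not what patients regard as worthwhile. Such a value could later be used to plan sample sizes or to interpret walking, activity and quality-of-life results in this population.

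**Working it through.** **The plan's own figure.** The Sample size section says "192 participants will be required to detect a mean 6MWD difference of 58 m (SD=111; α=0.05, 1-β=0.90"), with 20% attrition. Per arm, n = 2(1.960 + 1.282)² × 111² / 58² ≈ 77, so 154 in total, and 154 / 0.8 = 192.5 against 192 stated. The figure is reproduced, and about 154 participants are evaluable at 3 months. The article gives no figure for the ROC rule itself.

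**Where the cut-off falls with no association.** Let F be the distribution of change scores, the same in both rating classes. At cut-off c, sensitivity = 1 - F(c) and specificity = F(c). The squared distance to the corner is

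(1 - sensitivity)² + (1 - specificity)² = F(c)² + (1 - F(c))²,

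which is smallest at F(c) = 1/2. The rule therefore targets the median of the pooled change scores, which for a symmetric distribution is the mean.

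**Simulation A (6MWD).** From the document: 154 evaluable participants, equal arms, 58 m arm effect. Assumed: no mean change in usual care, within-arm SD of change 70 m, 50% rated improved, nobody excluded as worse. Pooled mean change = (58 + 0) / 2 = 29 m. The cut-off minimises the distance above.

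| Correlation of rating and change | Runs returning a value | Mean cut-off (95% range) | Mean AUC |
|---|---|---|---|
| 0 | 100% | 29 m (about -7 to 65) | 0.50 |
| 0.3 | 100% | 29 m (2 to 58) | 0.64 |
| 0.5 | 100% | 29 m (5 to 54) | 0.73 |
| 0.7 | 100% | 29 m (7 to 51) | 0.83 |

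**How far this depends on the assumptions.**

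- With 30% improved, the cut-off runs from about 32 m at zero correlation to about 50 m at 0.7. With 70% improved, it runs from about 28 m down to about 10 m. The constant 29 m belongs to the 50% split with nobody excluded.
- If usual care also gains 30 m, the pooled mean is 29 + 30 = 59 m, and the cut-off is about 59 m at zero correlation and also at 0.5.

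**Simulation B (a separate model).** Assumed: one common mean change of 20 m, SD 70 m, 40% rated improved, 15% rated worse and left out of the ROC.

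- At zero correlation a value was returned in 100% of runs: median 22 m, 5th to 95th percentile -8 to 51 m, sensitivity 0.53, specificity 0.54.
- Setting the mean change to 0, 10, 20 or 40 m gave medians of 1, 11, 21 and 42 m.
- The cut-off was positive in 50%, 72%, 89% and 99% of those runs respectively.

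**Effect of a condition on the AUC.** With A the AUC and n1, n0 the class sizes, SE² = [A(1 - A) + (n1 - 1)(Q1 - A²) + (n0 - 1)(Q2 - A²)] / (n1·n0), where Q1 = A/(2 - A) and Q2 = 2A²/(1 + A). In simulation B, A - 1.96·SE exceeded 0.5 in about 3% of runs at zero correlation (2% to 4% across the assumed inputs). It did so in 63% at correlation 0.3, 98% at 0.5 and 100% at 0.7.

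**The case against.** The strongest reply is that the same paragraph already plans the diagnostics. An uninformative rating would tend to show as a correlation near zero, flat group means and a ROC curve along the diagonal, and an attentive reader would notice. That stands in part: the checks exist, but nothing ties them to the declaration. The distribution-based estimate does not close the gap, because it contains no patient rating and cannot show whether the anchor was informative.

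A second reply is that thresholds and intervals belong in the SAP. The unseen SAP may indeed contain them. But the article states the decision rule in full and without condition, so the point concerns a rule as written, not a detail left out. A third reply, that a correlation of exactly zero is an extreme case, is fair; the documents do not say how strong the association will be.

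Three stronger readings might be inferred, and none is supported:

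- *That the rule always yields a plausible MCID.* It always yields a value. With no association some values are zero or negative: 91% to 95% were positive under simulation A's inputs with its improver split varied, and 50% to 99% as the mean change varied in simulation B.
- *That the reported value can never reveal whether the rating was informative.* The identical means hold only for the 50% split with nobody excluded. The article gives no proportion improved, and its classification leaves out participants rated worse.
- *That dependence on mean change is peculiar to an uninformative rating.* It is not, as the 59 m result at correlation 0.5 shows.

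**Conclusion.** The concern holds in limited form. As written, the rule declares an MCID for every measure whatever the evidence. With no association that value sits near the pooled mean change: about 29 m for 6MWD, with a 95% range of about -7 to 65 m. The rule attaches no interval that would show this imprecision.

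That every ROC curve has an upper-left point needs no assumption. The metre figures rest on an assumed SD of change of 70 m, assumed mean changes and assumed proportions improved, none of which the article gives, and on reading the upper-left corner as the point at least distance from it. This is an inexpensive improvement to one secondary objective. The primary comparison of 6MWD at 3 months is unaffected.

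**What to change.** Replace the decision sentence, in the protocol or the SAP, with wording such as:

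*For each measure and time point, the upper-left point will be reported as the anchor-based MCID only if the 95% confidence interval for the AUC lies above 0.5. It will be reported with the correlation between rating and change, the AUC and a bootstrap 95% confidence interval. Otherwise it will be stated that no anchor-based MCID could be established.*

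The trial statistician may also prespecify a minimum correlation. A value such as 0.30 would be a proposal and cannot be derived from the documents; it would reject about half of runs when the true correlation is 0.3.

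The cost is a few sentences and a bootstrap on data already planned. Some measures may end without an anchor-based MCID: in simulation B the AUC condition failed in 100% - 63% = 37% of runs at correlation 0.3. Those that are reported will show wide intervals; the sampling range in simulation A at correlation 0.5 is about ±(54 - 5)/2 ≈ 25 m. The condition does not remove the dependence of the cut-off on mean change or on the proportion improved, so both should be reported beside each MCID.

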### Primary outcome

The primary outcome is the difference in mean 6MWD in metres at 3 months between groups. This will be assessed by a self-paced 6 min walk test over a 60.96 m (200 foot) circuit.^38–40^ Pain intensity will be measured before and after the walk test using a standardised pain scale for claudication.^41^ The walk test will be completed twice, with the highest 6MWD used for analysis.

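### The SEM-based MCID takes its test–retest ICC from baseline and follow-up scores of all participants, so true change counts as measurement error and the MCID is expected to be inflated

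*Protocol article*

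**What the plan says.** The Statistical analysis section adds a second MCID method to the anchor-based one: "As a sensitivity analysis, the MCID will be also calculated using a distribution-based approach". It applies to everyone: "The SE of measurement for all participants scores will be used to estimate the MCID based on the following equation", the equation being σ₁√(1−r) with σ₁ the baseline SD. The section says that r "represents the intraclass correlation coefficient, which is a measure of the test–retest reliability of the scale", and then fixes the data for it: "The intraclass correlation coefficient will be calculated using the baseline and follow-up scores for each participant". The result is used directly: "Using this method, 1 SE of measurement represents the estimated MCID".

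Three other parts of the article bear on this:
- Outcome assessment and Interventions: follow-up is at 3 and 6 months after randomisation, and MOSAIC sessions fall in weeks 1, 2, 6 and 12. Table 3 lists the 6MWD at baseline and 3 months only.
- Secondary outcome measures: an unchanged category is already defined for the global rating. "Scores of −1, 0 and 1 will be considered no change, scores of 2–3 small improvement and scores of 4–7 substantial improvement".
- Primary outcome: "The walk test will be completed twice, with the highest 6MWD used for analysis".

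**The concern.** Test–retest reliability describes how closely repeated scores agree when the person's true state is the same on both occasions. The plan names that quantity and then computes another one: the agreement of scores 3 or 6 months apart, in a trial designed to move one arm. Improvement, deterioration and the difference between arms all pull the two scores apart, and the formula treats the whole of that spread as measurement error.

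Controls are not a stable group either, because the Usual care section allows supervised exercise, drug treatment and revascularisation.

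MCID estimation is a stated secondary objective. If the SEM-based value contains true change, neither agreement nor disagreement with the anchor-based value can be interpreted. An inflated figure could also be taken up by later trials.

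**Working it through.** **Figures in the plan.** The article gives no ICC, SEM or MCID value to reproduce. The two numbers used below come from the Sample size section, which does reproduce. With two-sided α of 0.05 (sidedness is not stated) and 90% power, n per arm = 2 × [111 × (1.960 + 1.282) / 58]² ≈ 76.97. Then 2 × 76.97 / 0.8 ≈ 192.4, against the stated 192.

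**Inputs.**
- From the document: arm difference 58 m; 1:1 allocation (96 per group).
- Assumed: baseline SD σ₁ = 111 m (the document gives this SD only as a sample-size input); true reliability r₀ = 0.80, 0.90 or 0.95; SD of individual true change around the arm mean s = 0, 30 or 60 m, independent of baseline; no mean change in controls.

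**Formulas.** Variance of true change over all participants: v_d = 0.5 × 0.5 × 58² + s² = 841 + s². Mean change: 0.5 × 58 = 29 m. With v₁ = 111² = 12,321, covariance = r₀ × 12,321 and v₂ = 12,321 + v_d:
- ICC (consistency) = 2·cov / (v₁ + v₂)
- ICC (agreement) = 2·cov / (v₁ + v₂ + 29²)
- SEM = 111 × √(1 − ICC)

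Because σ₁ is the baseline SD, the distortion enters only through r.

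**Worked case, r₀ = 0.90, s = 0.** Without true change, SEM = 111 × √0.10 = 35.1 m. Under the planned rule:
- Consistency: 22,177.8 / 25,483 = 0.870, so SEM = 40.0 m (+14%).
- Agreement: 22,177.8 / 26,324 = 0.842, so SEM = 44.1 m (+26%).

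**All scenarios** (SEM in metres, consistency / agreement):

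| r₀ | No true change | 58 m arm effect only | plus s = 30 m | plus s = 60 m |
|---|---|---|---|---|
| 0.80 | 49.6 | 52.8 (+6%) / 55.6 (+12%) | 55.8 (+12%) / 58.3 (+17%) | 63.0 (+27%) / 64.8 (+31%) |
| 0.90 | 35.1 | 40.0 (+14%) / 44.1 (+26%) | 44.3 (+26%) / 47.8 (+36%) | 54.1 (+54%) / 56.5 (+61%) |
| 0.95 | 24.8 | 31.7 (+28%) / 36.9 (+49%) | 37.3 (+50%) / 41.5 (+67%) | 49.0 (+98%) / 51.8 (+109%) |

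A simulation of two million participants for r₀ = 0.90 and s = 30 m gave 44.3 and 47.8 m, matching the formulas.

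**Does the direction depend on the assumptions?** A shift shared equally by everyone lowers only the agreement ICC. Change that differs between arms or individuals lowers both forms. A strong positive correlation between change and baseline could offset this in principle. In the r₀ = 0.90, s = 30 m scenario, however, correlations from −0.5 to +0.5 still gave an SEM of 42 to 51 m against 35.1 m.

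**The case against.** The strongest reply concerns importance. This is a sensitivity analysis for the last-listed secondary objective. The primary regression, the other treatment comparisons and the anchor-based MCID do not use it. That stands, and it limits the severity.

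The second reply is that the size of the bias is not knowable from the document. The ICC form, the true reliability and the spread of true change are all unstated. That also stands. A reader who takes reliability 0.95 and an agreement ICC might infer that the MCID must be at least 1.5 times too large, but that is only the upper part of the range.

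Three further inferences are tempting, and the document does not support them:
- That this is the only check on the anchor-based value. The plan also correlates self-rated with measured change and compares mean change across the no-change, small and substantial improvement groups.
- That the trial's effect will be judged against an MCID which it has itself inflated. The primary result is reported as a mean difference with a 95% CI, and nothing in the article measures it against this MCID.
- That the ROC cut-off is wrong in the same way because its changed group pools small and substantial improvement. That contrast is an explicit, referenced choice. It keeps more participants, and the small-improvement mean is reported separately. Preferring ratings of 2–3 alone is a design preference.

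It might also be said that the analysis plan, not shown here, could settle the detail. It may settle the ICC form. The data source for r, however, is stated outright in the article and conflicts with the definition in the sentence before it.

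**Conclusion.** The point holds. The article defines r as test–retest reliability and then computes it from data in which true change is expected, so the SEM-based MCID is expected to be inflated and does not serve as a valid sensitivity check. With a baseline SD of 111 m and true reliability between 0.80 and 0.95, both assumed, the 58 m arm effect alone inflates the 6MWD value by about 6% to 49%. An assumed individual-change SD of 60 m takes the upper end to about 109%. These are ranges under assumptions, not estimates of the error. The same reasoning applies to the four questionnaire measures, for which the document gives no figures. Severity is low to moderate.

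**What to change.** For each of the five measures, estimate r only in participants whose global rating at that follow-up is −1 to +1, and state the ICC form (consistency or agreement). The rating asks about change since the previous test, so at 6 months the two scores should span the interval that the rating covers. Restricting to the usual care arm instead would not be enough, since controls may change too.

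For the 6MWD, keep both walk distances and report an ICC from the paired tests as a supplementary figure. It should not be presented as the correct SEM. It probably gives a lower bound, because it leaves out variation between days and months. It also describes single walks, whereas the analysed score is the better of two, and the article does not state the interval between them.

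The change needs wording only and uses planned data, provided both walk distances are retained. The cost is a smaller sample for the ICC and so a less precise r, which should be reported with its confidence interval.
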